**Study B:**

In the sub study we will also collect additional samples to research what the influence of breastfeeding is on immune development, compared to other routes that are enrolled in the transfer of maternal immunity to the neonate. This will be done in a subgroup of 20 mother-child dyads. The samples that we will collect are cord blood samples, a maternal blood sample and an amniotic fluid sample. Jacobino et al. showed that antibodies retrieved form human amniotic fluid protected mice pups against RSV-infections (Jacobino2016). Very little is known about the protective value antibody titters in cord blood. Active placental transport of maternal antibodies to the neonatal blood has been described, but little is known about the effectiveness of these antibodies (Kohler1966). To obtain more insight in the effect of the antibodies that are being transferred by breastfeeding, we will compare the effect of breastfeeding to the antibodies in cord blood and amniotic fluid. To evaluate the effect of the maternal Bordetella pertussis vaccination on (pertussis-specific) immune development in children, we will also collect saliva samples at 1 week, 1 month, 3 months, 6 months and 12 months postpartum. Saliva samples offer an ideal method to evaluate the (Bordetella-pertussis specific) immune development during the first year of life since saliva antibody titters correlate well with serum titters but saliva samples are considered to be non-invasive.

**Study C:**

In an additional sub-study (afterwards called study C) we would like to expand the current study design to assess the role of the maternal diet and infants’ intestinal microbial development on the risk of developing respiratory tract infections in the first year of life.

Breast milk is a very variable body fluid influenced by many maternal and environmental factors (Munblit et al., 2014). The maternal diet during lactation is one of the factors for which there are strong suggestions that it influences breast milk composition (Bravi et al., 2016). A Finnish observational cohort study with normal weight (n=49) and overweight (n=51) women found an association of a 34% percent increase of n-3 fatty acids (FA) in a 3 month postpartum-breast milk sample for women who consumed fatty fish in the two days before the sample collection. The same study found a significantly increased n-6 FA concentration in breast milk of women who consumed vegetable-oil-based-spreads on a regular basis. Consumption of high-fat dairy products was associated with a significantly increased concentration of short-chain fatty acids (SCFAs) (Mäkelä et al., 2013).

As elaborately discussed in the background for study A, breastfeeding protects against respiratory tract infections in infants, including RSV infection. Apart from antibodies and HMOs, also FAs have antiviral and -microbial properties. Especially medium chain saturated, such as lauric acid (C12:0), and long chain unsaturated FAs, such as linoleic acid (C18:2) appear to be potent in affecting the lipid coating of viruses (Isaacs, 2005; Thormar et al., 1987). In addition, macrophages exposed to omega-3 FA docohexaenoic acid (DHA) (C22:6) and omega-6 FA arachidonic acid (C20:4) have an increased capacity to phagocytise and have an increased microbicidal activity. Endogenous fatty acid production by the mammary gland is limited to a chain length of 14 (*de novo* FAs), therefore, the long chain FAs are derived from the diet (Hachey et al., 1989; Nasser et al., 2010), indicating the relevance of the maternal diet in relation to risk of RTIs for infants.

Very limited research has been performed focusing at the association between maternal diet and HMO composition in breast milk. A prospective observational birth cohort did not find a correlation between maternal diet quality and total HMO concentration nor for individual HMOs (after correction for multiple comparisons) in breast milk (Azad et al., 2018). However, the study of Azad and colleagues assessed the maternal diet by means of a food frequency questionnaire (FFQ) during late pregnancy, while the breast milk sample was collected 3-4 months postpartum. Another prospective cohort did find a positive correlation between fruit intake and unsaturated fatty acids consumed on the day before breast milk sampling, with various (sulfonated) HMOs in breast milk. Even more, monosaccharide 5-N-glycolyl-neuraminic acid (Neu5Gc) was identified in all breast milk samples. Notably, this monosaccharide cannot be synthesized endogenously and is diet-derived (e.g. from red meat) (Quin et al., 2020).

HMOs are of increasing interest because of their antimicrobial and antiviral capacity on one hand, and prebiotic capability on the other hand. HMOs prevent viruses to adhere to epithelial surfaces, by mimicking viral receptors or block receptors on epithelial cells (Morozov et al., 2018). Their prebiotic effect is achieved by the fact that specific strains of the commensal species Bifidobacteria and Bacteroides are able to metabolize HMOs and therefore are in favour in competition with strains unable to metabolize HMOs, such as *E. coli* and *Enterococci* (Ayechu-Muruzabal et al., 2018)*.*

Accumulating evidence shows that the intestinal microbial composition mediates the lung microbiota composition, also referred to as the gut-lung axis. The presence of microbiota in the respiratory tract, and more importantly the significant role it has in the pathogenesis of respiratory tract infections, is only studied for about a decade. Schuijt and colleagues performed a mice study for which mice were treated with antibiotics, after which *S. pneumonia* was administered intranasally. It was found that the antibiotic-treated mice had a.o. an increased mortality, inflammatory markers and an increased bacteria outgrowth. The significant role of the intestinal microbiota specifically was shown by normalizing the bacterial counts and IL-10 and TNF-α levels in the respiratory tract after fecal microbiome transplantion (FMT) (Schuijt et al., 2016). A different mice study of Kanmani and colleagues showed the relevance of the lung microbiota in the context of respiratory tract infections. Mice were intranasally administrated with *Corynebacterium pseudodiphteriticium,* a bacterium which is a commensal in the respiratory tract microbiota. The priming appeared to reduce the susceptibility to a primary RSV infection by modulating the toll-like receptor 3-mediated antiviral inflammatory response (Kanmani et al., 2017). The microbiota community present in the lung also seems to be relevant for the development of asthma. Comparison of the lung microbiota of both asthmatic adults and children shows that there was an increased presence of pathogenic Proteobacteria compared to the healthy controls (Hilty et al., 2010). Remot and colleagues performed a study with mice, for which they isolated several strains from the lung microbiota of healthy mice. The authors showed that intranasal administration of isolated strain to neonatal mice influenced the asthmatic immune response towards a house dust mite challenge (Remot et al., 2017).

Considering the influence of HMOs on the intestinal microbial development in infants, and the careful associations between intestinal microbial composition and risk of developing of RTIs and/or asthma, the pathway from maternal diet to breast milk composition to intestinal composition to eventually risk of developing RTIs and/or allergies is very relevant.

Taking together, although there are strong suggestions for the influence of maternal diet on breast milk composition, the scarcity of high quality studies and diversity in study design restrain the ability to draw strong conclusions. In addition, there is a lack of studies linking the maternal diet and associated breast milk composition to the gut health of the infant resulting in protection against respiratory infections and/or the development of allergies. There is a vast need for an observational study with a bigger sample size, which is also based on a power calculation (Bravi et al., 2016). Therefore, we plan to perform a substudy within the PRIMA human milk cohort. In this cohort (n=250), we will additionally assess the maternal diet, and collect feces and saliva of the infant. This study design allows to not only link the short- and long-term influence of maternal diet to breast milk composition, but also the clinical health outcomes in infants, with Medically Attended Respiratory tract Infections during the first year of life as main study parameter. Even more, the influence of the maternal diet

and an infant’s antibody repertoire on intestinal microbial composition, and subsequently on the risk of developing RTIs is explored.

# OBJECTIVES

**Study A:**

Primary objective:
To measure to what extent 2’FL human milk oligosaccharides are protective against medically attended respiratory tract infection during the first year of life.

Secondary objective 1:

To identify which components, or combination of components, in human milk are protective against any parent-reported, physician reported infections during the first year of life.

Secondary objective 2:

To identify which components, or combination of components, in human milk are protective against the development of parent-reported, physician reported allergies during the first year of life and.

Secondary objective 3:

To identify which immunological components (antibodies, immune cells) in human milk, cord blood and amniotic fluid are protective against any parent-reported, physician reported infections during the first year of life.

Secondary objective 4:

To obtain insight in the gut discomfort and crying of infants in the first 6 months of life.

**Study B:**

Secondary objective 5:

To describe antibody concentrations in compartments relevant to materno-fetal antibody transfer. We will define the association between maternal serum, breast milk antibodies, cord blood, amniotic and infant antibodies over time. This study is performed while maternal pertussis vaccination is introduced. We will therefore analyse total and pertussis-specific antibody concentrations.

**Study C:**

Secondary objective 6:

To identify the long-term and short-term influence of the maternal diet on the breast milk composition.

Secondary objective 7:

Link the long-term and short-term influence of the maternal diet to the clinical outcome of respiratory tract infection during the first year of life.

Secondary objective 8:

To derive hypotheses about potential mechanisms if the maternal diet-influenced components in human milk are protective against respiratory tract infection during the first year of life.

Secondary objective 9:

To identify the association between long-term and short-term influence of the maternal diet on the microbiota composition of a 3-month old infant, and its consequence for the risk of developing respiratory tract infections in the first year of life.

Secondary objective 10:

To identify the antibody repertoire and viral genome in saliva samples from 3 month-old infants.

Secondary objective 11:

To link the antibody repertoire in saliva samples with antibody repertoire in feces and microbiota composition, and how this relates to the risk of developing respiratory tract infections in the first year of life.

#
[figure not shown]
STUDY DESIGN

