**Study C:**

Secondary objective 5:

To identify the long-term and short-term influence of the maternal diet on the breast milk composition.

Secondary objective 6:

Link the long-term and short-term influence of the maternal diet to the clinical outcome of respiratory tract infection and/or allergies during the first year of life.

Secondary objective 7:

To derive hypotheses about potential mechanisms if the maternal diet-influenced components in human milk are protective against respiratory tract infection and/or of allergies during the first year of life.

Secondary objective 8:

To identify the association between long-term and short-term influence of the maternal diet on the microbiota composition of a 3-month old infant, and its consequence for the risk of developing respiratory tract infections and/or allergies in the first year of life.

Secondary objective 9:

To identify the antibody repertoire and viral genome in saliva samples from 3 month-old

Secondary objective 10:

To link the antibody repertoire, viral genome load and possible other immune markers in saliva samples with feces microbiota composition, and how this relates to the risk of developing respiratory tract infections in the first year of life.

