**Main study parameters/endpoints:**

The main study parameters/endpoints of study A will also account for sub-study C.

Additionally, a main study parameter is the diet of lactating women. The dietary pattern (long-term) will be assessed by a food frequency questionnaire (FFQ) at 2 month and 4 month post-partum. Additionally, we will assess the short-term influence of the diet on breast milk composition by a 24-h recall on the day before the collection of a 1-month and 3-month human milk sample.

In addition to the questionnaires, we will also collect samples both from the mother (human milk) as from the child (saliva and feces):

In the collected human milk samples (1 week, 1 month, 3 and 6 months postpartum) we will perform additional analyses, such as to measure fatty acid composition, protein and amino acid composition, fat- and water-soluble vitamins and other fibres (than HMOs).

The feces will be collected from infants at 3 months postpartum. The feces will be analysed for microbial composition.

The saliva will be collected from infants at 3 months postpartum. The saliva will be analysed for the antibody repertoire and viral genome.

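### Study C relates 3-month stool and saliva markers to infection over the whole first year, so infections that precede the sample, and may have altered it, count as outcome

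*Protocol*

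**What the plan says.** The Protocol fixes both the sampling time and the outcome window.

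- **Sampling.** The Summary (Study C) states "The feces will be collected from infants at 3 months postpartum" and "The saliva will be collected from infants at 3 months postpartum". Section 3 (Study C) justifies the time point by the expected effect of milk and by the later start of solid food. Section 5.2 has a parent collect the saliva in the week before the 3-month visit.
- **Microbiota.** Section 2, Study C, secondary objective 9 names the "microbiota composition of a 3-month old infant, and its consequence for the risk of developing respiratory tract infections in the first year of life".
- **Salivary antibodies.** Objective 11 links them with stool findings and asks "how this relates to the risk of developing respiratory tract infections in the first year of life".
- **Viral genome.** Section 2, objective 10 is descriptive: "To identify the antibody repertoire and viral genome in saliva samples from 3 month-old infants". Summary objective 10 goes further. It sets out "To link the antibody repertoire, viral genome load and possible other immune markers in saliva samples with feces microbiota composition" and then relates these to first-year infection risk.
- **Endpoint.** The Summary (Study C) says "The main study parameters/endpoints of study A will also account for sub-study C". Section 5.1.1 defines that endpoint over the whole first year of life.

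Nowhere does the Protocol start the count at sampling, set aside infections in the first three months, or adjust for them.

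**The concern.** Time order is wrong for part of the outcome. An infection at six weeks comes before the 3-month sample. It can leave antibodies or viral genome in saliva, and the infection or its treatment can change the stool microbiota. If that same infection counts in the outcome, a marker that merely records past illness will be associated with infection risk.

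The direction depends on how the marker responds. A marker raised by earlier infection will look harmful, and a truly protective one may lose its association or have it reversed. By symmetry, a marker lowered by earlier infection will look protective. Since Study C looks for a pathway from diet through microbiota to later infection, this error could supply a plausible but false result.

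**Working it through.** **Stated figure.** The point rests on time order. The Protocol gives no power or error rate for these objectives, so there is no figure to reproduce.

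**Time order.** Marker time: month 3, once. Outcome window: months 0 to 12. Share of calendar time before the sample: 3/12 = 25%. This is also the share of events only if infections are spread evenly over the year, which the Protocol does not say.

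**Size of the effect.**

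Input from the Protocol: n = 250 (Introduction, Study C; Section 4.4 asks for at least 247).

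Assumed inputs, because the Protocol gives none:
- rate r = 0.3 to 1.0 infections per child-year;
- share s = 10% to 25% of infections before month 3;
- shift g = 0.2 to 1.0 SD in the marker after any early infection.

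Model:
- early count E ~ Poisson(r·s);
- later count L ~ Poisson(r·(1−s));
- marker M = N(0,1) + g·1(E>0), standardised. M has no effect on L.

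The probability of at least one early infection is 1 − exp(−r·s). It is 1 − exp(−0.03) = 3.0% at the low end and 1 − exp(−0.25) = 22.1% at the high end.

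Poisson regression was fitted to E+L (full year) and to L (from sampling), with Pearson-scaled or robust standard errors and two-sided 5% tests. The table gives the share of significant results. The spurious full-year rate ratio per SD is in brackets where it was recorded.

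| r | s | g | Full year | From sampling |
|---|---|---|---|---|
| 0.3 | 10% | 0.5 | 8.1% (1.05) | 5.7% |
| 0.3 | 10% | 1.0 | 13.1% (1.10) | 5.0% |
| 0.3 | 25% | 0.5 | 18.1% (1.13) | 3.5% |
| 0.3 | 25% | 1.0 | 48.5% (1.25) | 5.9% |
| 1.0 | 10% | 0.5 | 12.4% (1.05) | 5.9% |
| 1.0 | 10% | 1.0 | 29.8% (1.09) | 5.4% |
| 1.0 | 25% | 0.2 | 9.1% | 4.5% |
| 1.0 | 25% | 0.5 | 33.3% (1.10) | 5.7% |
| 1.0 | 25% | 1.0 | 81.3% (1.19) | 4.8% |

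The 0.2 SD row used 1,000 simulated cohorts and the others 1,500. With no shift (g = 0) the full-year analysis gives 4 to 5%, as it should. Repeat runs with other seeds gave the same picture, with the from-sampling count reaching about 7%.

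**Is restriction enough?** Let infants differ in susceptibility (gamma frailty, variance 0.5; r = 1.0, s = 25%):

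| g | Full year | From sampling | From sampling, adjusted for E |
|---|---|---|---|
| 0.5 | 36.9% (1.13) | 8.5% (1.04) | about 4–7% |
| 1.0 | 89.6% (1.27) | 16.1% (1.09) | about 4–7% |

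The last column gives the range over separate runs. Starting the count at sampling removes the direct error. Adjustment for earlier infections removes what is left through shared susceptibility.

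**A truly protective marker.** Take a true rate ratio of 0.85 per SD with r = 1.0, s = 25% and no frailty. The full-year analysis returns 0.97 at g = 0.5 and 1.06 at g = 1.0. Counting from sampling returns 0.85 in both cases.

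**The case against.** The strongest reply is that the Protocol specifies no model for these objectives. Section 7.1 describes Poisson regression for 2'FL, and Section 7.2 extends it to allergies and total infections. The only Study C method named is classification, with support vector machines as an example, in Section 4.4. Window start, offset and adjustment usually belong in a statistical analysis plan, and the first year could be read as only the end of follow-up. This stands in part: no wrong model has been written down. However, the whole-year window is in the objectives and in the endpoint carried into Study C. An analyst who follows them would count the early infections, so the objectives themselves need the correction.

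Three stronger readings are tempting, and the documents do not support them.

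- *All three markers are treated as causes.* Only objective 9 speaks of a consequence, and it concerns microbiota. Objective 11 speaks of a relation, and the Introduction calls these links exploratory.
- *Viral genome is a predictor throughout.* Section 2 only describes it, and the Summary statement "The saliva will be analysed for the antibody repertoire and viral genome" is about a laboratory measurement. The link to infection risk appears only in Summary objective 10.
- *A false-positive rate of 30% or 80% should be expected here.* The inputs are unknown. The only incidence figure, 10% with a medically attended lower respiratory infection (Section 4.4), is for a narrower outcome.

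**Conclusion.** The concern holds for stool microbiota and salivary antibodies, and for viral genome load only if the Summary's link to infection risk is kept. The stated outcome window begins before the marker is measured, and nothing in the Protocol corrects for this.

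The size is uncertain. Across the assumed ranges the false-positive rate of the full-year count runs from about 8%, little above nominal, to over 80%. Counting from sampling brings it to roughly 4 to 8%. With between-infant differences in susceptibility, about 8 to 17% remains in the settings shown unless earlier infections are adjusted for. These figures show a mechanism and its range and do not predict what this cohort will find.

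The point is confined to secondary objectives of a substudy. The primary 2'FL objective, the data collection and the sample size are untouched. It should still be settled before analysis, because the stated window can bias the answer and the remedy is nearly free.

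**What to change.** In Section 2, objectives 9 and 11, define the outcome as respiratory tract infections after the stool or saliva sampling date through 12 months. Then:

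- where a count model is used, include log person-time from sampling as offset;
- adjust for infections before sampling;
- report any relation between the markers and earlier infections as association only;
- bring the matching Summary objectives into line, and reconcile Summary objective 10 with Section 2, objectives 10 and 11, on whether viral genome load is related to infection risk. If it is, the same window applies.

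Cost: wording only. The two-weekly questionnaires (Section 5.2) already place episodes before or after sampling, so no new data or visits are needed. Events before 3 months leave these secondary analyses as outcomes. That is about a quarter if events are spread evenly (for example, 62.5 of 250 expected events at 1 infection per child-year, 250 × 1 × 0.25) and fewer if early infections are rarer.

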**Study A**

This cohort concerns a prospective observational cohort study. A retrospective collection of data collection or sample collection would not be useful for this cohort. Retrospective data collection will decrease the validity of data collected from parents through questionnaires. Moreover, since the composition of breast milk differs in time postpartum, samples have to be collected at certain time points in order to elucidate its precise and unique composition.

**Study B**

Saliva samples will be collected at 1 week, 1 month, 3 and 6 months because of pragmatic reasons. The 12 months sample will be collected since the last vaccination during the first year of life against Bordetella pertussis is offered at 11 months (the next vaccination is offered at 4 years in the Netherlands) (Rijksvaccinatieprogramma).

**Study C**

A 24h recall is filled in on the day of collection of the 1 and 3 month breast milk sample, to determine the short-term effect of maternal diet on breast milk composition. The FFQ is filled in at 2 and 4 months, to determine the long-term effect (dietary pattern) on breast milk composition. The 4 month FFQ is a repetitive measurement to evaluate whether the maternal diet has changed since 2 months, and therefore also can be linked to the 3 month breast milk sample. A change in dietary pattern is conceivable because, for example, the mother has stopped breastfeeding and/or maternity leave from work has ended.

Feces and saliva are collected at 3 months because at this time point the effect of the breast milk composition is expected to more significant that at 1 month or 1 week postpartum. The 3 month time point is also more suitable than the 6 month time point because by that time, infants may have received solid foods aside of breast milk and/or infant formula.

